Overview of the questions asked in the phase 1 questionnaire (version completed by individuals with epilepsy). Individuals affected by people with epilepsy completed a version with alternate wording appropriate to their perspective.Demographics:Year of birthSex at birthDescribe the type of epilepsy or seizures you have and the symptoms that you experience during a seizure. *The intention of asking this question is to determine if the symptoms that the person with epilepsy experiences during a seizure (such as losing consciousness, muscle control, etc) influences their anxiety.*Scenes:List up to 5 scenes (such as situations, locations, or environments) where you feel anxiety related to your epilepsy or seizures. Next to the open-ended spaces to list each scene, participants are asked to rank their avoidance behavior from the following options:Avoid completelyOften avoidSometimes avoidDo not avoid (but still feel anxious)To ensure that the 360° videos, which will be recorded in phase 2, are realistic and resemble the scenes from the person with epilepsy’s point of view as closely as possible, participants are asked to provide detail about the scene that causes the greatest amount of anxiety, as if they were designing a scene for a movie from their perspective. Participants are prompted to do so by asking:What do you see, hear, and feel?What are you and others doing in this scene?What in particular about this scene makes you anxious?What changes to this scene would (1) increase and (2) decrease your anxiety? *Since ET often involves exposing people to their fears in a hierarchical manner, the VR-ET program will involve exposing participants to levels of the scenes reported in phase 1. Although subject to change based on phase 1 results, exposures will have 3 levels. This question about how changes to the scene may increase or decrease anxiety will help determine the different films that should be recorded to represent the fear.*Participants are given the option of describing additional scenes.Closed-ended questions: Participants are provided with a series of scenes developed based on the researchers’ knowledge of epilepsy or seizure-related anxiety, as well as evidence from the literature [1,25] and asked to rate how likely these scenes would generate epilepsy- or seizure-related anxiety. The rating options are as follows: strongly agree, somewhat agree, somewhat disagree, strongly disagree, and prefer not to say. The specific scenes are listed below. Ratings on these scenes will also help to inform phase 2 recordings.On a subway platformOn a subway trainOn a busOn stairs or elevated platformsIn a washroom or other place with hard surfacesAt a shopping centerCompletely aloneWith a few people that I know (but not well)With a few people that I have a close relationship withAt a large social gathering or party where I only know a few peopleAt a large social gathering or party where I know some or all peopleSurrounded by complete strangers in a public settingGoing for a walk outsideExercising with gym equipmentIs there anything else you’d like to share about your epilepsy- or seizure-related anxiety?

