**Proposed diagnostic protocol for epilepsy-specific anxiety disorders [1]**
Hingray et al [1] suggested a diagnostic enquiry for 4 proposed anxiety disorders specific to epilepsy: anticipatory seizure anxiety, seizure phobia, epileptic social phobia, and epileptic panic disorder. They also suggested an assessment for symptom severity of each of these disorders and an evaluation of avoidance behaviors.Note: On the basis of responses to the assessment by Hingray et al [1], individuals who appear to have epileptic panic disorder according to a clinical neuropsychologist will be excluded from the study.

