##### Postintervention (T2)

One week after completing the VR-ET intervention, the participant will answer several assessments (Table 1 and Textbox 6), specifically EASI; PSS; Igroup Presence Questionnaire (IPQ) [44]; and the System Usability Scale (SUS) [45]. The proposed diagnostic protocol for epilepsy-specific anxiety disorders [1] will not be repeated at T2 and will instead inform some of the open-ended questions that will be asked in the semistructured exit interview that will take place over telephone or video conferencing (Textbox 6). The interview will be conducted either by an ETS or a member of the research team and will aim to gather additional feedback about the participants’ experience. For example, participants will be asked to provide feedback on their experiences with the various devices, the subjective impact of the therapy, and what may be improved about the program and ET scenarios. Similar to T0, the only in-person aspect of T2 will take place when a member of the research team goes to the participant’s residence to collect the VR equipment.

Outcome measures at T2.Repeat: Epilepsy Anxiety Survey Instrument and Perceived Stress Scale

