#### Phase 3 Data Analysis

As both quantitative and qualitative data will be collected in phase 3, a mixed methods approach will be used. Quantitative statistical analyses will be performed using the MiniTAB statistical package [46] and SPSS software (version 27.0; IBM Corp) [47]. To investigate the normal data distributions of the dependent variables, ranges of skewness and kurtosis will be determined. The Kolmogorov-Smirnov and the Shapiro-Wilk tests will also be performed to evaluate statistical significance (mean, 95% CI) and normality of the distributions. In addition, Cronbach *α* will be performed for each self-report questionnaire’s subscales. To explore sociodemographic features, frequencies, means, and standard deviations will be calculated.

To explore the effects of VR-ET, data collected at T0 and T2 will be compared. Clinically significant effects of the intervention will be investigated using the Jacobson-Truax method, based on the measures’ clinical cut-offs (Table 2). Moreover, SUDS scores (before the exposure, immediately after the exposure, and 10 minutes after the exposure) collected every day of T1 will be compared with each other. Participants’ SUDS scores that are recorded immediately after the exposure may be lower than their anticipatory anxiety levels, and if so, this may encourage the participant to do the next exposure. We will also consider our study to be successful if participants’ SUDS scores remain high in the first postexposure SUDS test but decrease at the 10-minute postexposure SUDS test. However, the study may still be deemed successful with unchanging SUDS scores if participants have reduced anxiety and engage in fewer safety-seeking behaviors after completing VR-ET, as based on T2 findings.

Using thematic analysis, qualitative responses to assessments and interviews will be assessed by the research team and then reported as frequencies using the procedure outlined by Braun and Clarke [48]. The constant comparison method will be used to analyze the responses to the open-ended questions asked at T0 and T2 [49].

**Table 2 table2:** Clinically significant scoring for the phase 3 assessments.

		Items	Range	Scores	Citation

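### The success route that counts fewer safety-seeking behaviours has no assessment described as covering avoidance or safety-seeking at both T0 and T2

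*Protocol article*

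**What the plan says.** Phase 3 Data Analysis compares T0 with T2 and describes several patterns that would count as success. One of them applies when the SUDS scores do not move: "the study may still be deemed successful with unchanging SUDS scores if participants have reduced anxiety and engage in fewer safety-seeking behaviors". The source for that judgement is given only in general terms ("safety-seeking behaviors after completing VR-ET, as based on T2 findings"), and no instrument is named.

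Textbox 3 lists the T0 assessments. For the diagnostic protocol for epilepsy-specific anxiety disorders it says of the cited authors: "They also suggested an assessment for symptom severity of each of these disorders and an evaluation of avoidance behaviors". Table 1 ticks this tool once, at T0. Postintervention (T2) says that it "will not be repeated at T2 and will instead inform some of the open-ended questions that will be asked in the semistructured exit interview". The instruments that are given again are listed in Textbox 6: "Repeat: Epilepsy Anxiety Survey Instrument and Perceived Stress Scale".

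The exit-interview topics in Textbox 6 are usability and training, the realism of the scenes, the effect on anxiety, delivery and format, and general experience.

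**The concern.** The criterion is directional and needs a baseline: behaviours can only be fewer relative to an earlier observation. The clause also carries weight, because it can turn an unchanged SUDS result into a success. That calls for a component measured in the same way before and after treatment.

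The schedule does not provide this. The assessment that touches on avoidance is collected before treatment and then set aside, and the scales that are repeated are described as measuring something else. The judgement would then fall to what participants say in an exit interview conducted by the exposure therapy specialist or a team member, in a study that the Limitations section describes as unblinded and without a control group. Impressions gathered that way tend to favour the treatment.

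The behaviour is also central to the rationale. The Background section treats safety behaviours, with avoidance as an example, as what keeps the anxiety going. A pilot meant to inform a larger trial would end without a paired observation of it.

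**Working it through.** There is no formula or stated figure to reproduce. The check sets the success rule against the Phase 3 schedule, using Table 1, Textboxes 3 to 6 and the text of T0, T1 and T2.

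| Assessment | T0 | T1 | T2 | What the article says it covers |
|---|---|---|---|---|
| EASI (contains the brEASI) | yes | no | yes | features and severity of epilepsy-related anxiety |
| PSS | yes | no | yes | perceived stress |
| Diagnostic protocol | yes | no | no | four disorders, symptom severity, avoidance |
| Background questionnaire | yes | no | no | demographics, technology, epilepsy and anxiety history, medication; no avoidance item listed |
| VRISE | yes | no | no | motion sickness |
| SUDS | no | daily | no | distress around the exposure |
| Fast Motion Sickness Scale | no | daily | no | motion sickness |
| Coping-mechanism use | no | daily | no | use of the supplied coping techniques |
| IPQ, SUS | no | no | yes | presence, usability |
| Interview | yes | no | yes | T0: choice of scene set and order, review of coping techniques; T2: the feedback topics above |

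1. Instruments described as evaluating avoidance: 1 (the diagnostic protocol), at T0 only.
2. Questionnaires given at both T0 and T2: 2 (EASI and PSS). Neither is described as covering avoidance or safety-seeking.
3. Overlap of 1 and 2: 0. With a target of 5 participants, 0 of 5 would have a repeated assessment described as covering the behaviour.
4. The interview is the only other element at both visits. The T0 interview serves to choose the scenes and their order and to review coping techniques. The Limitations section adds that it will give more insight into participants' fears. None of this is described as a baseline of safety behaviours, and the T2 topics do not name them.
5. Table 2, which lists the scoring used for clinical significance, contains EASI, brEASI and PSS and nothing on avoidance.
6. A rating of the right kind exists elsewhere. In the Phase 1 questionnaire (Textbox 1), "participants are asked to rank their avoidance behavior from the following options", with four levels from complete avoidance to none. It is not a Phase 3 assessment, so it gives no Phase 3 change.

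**The case against.** The strongest reply is that the design is mixed methods and the measure is qualitative, not absent. The sentence that stops the diagnostic protocol at T2 also says it will shape some exit-interview questions. Phase 3 Data Analysis plans constant comparison of open-ended answers from T0 and T2, and thematic results reported as frequencies. This stands. A reader might infer that the change cannot be measured at all, and the article does not support that.

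Three other strong readings also fail:

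- That no participant will have paired severity data. The EASI is given at both visits and is described as assessing severity.
- That a scored baseline is set against an unscored T2 answer. The article does not say the diagnostic protocol yields a score.
- That the T2 answers are necessarily recalled. No interview wording is given, and questions about current behaviour would fit the text equally well. Nor can the article settle whether any EASI item touches avoidance.

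It is also fair to say that an interview guide is commonly left to the full protocol, and its absence is not the point here. The article itself fixes both the success rule and the decision not to repeat the tool, and the two do not fit. A later analysis plan cannot recover data that were not collected at T2. If the guide does hold matched questions for both visits, the article needs only to say so.

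Finally, the clause is permissive and also requires reduced anxiety, and Phase 3 is a feasibility pilot that disclaims clinical efficacy. That limits the consequence but does not remove the mismatch, since the protocol still words this as a route to success and names effect sizes in its primary objective.

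**Conclusion.** The point holds in a limited form. The safety-seeking component of this success route has no assessment, described as covering it, that is repeated at T0 and T2. What remains is self-report from open-ended exit questions that are not identified, gathered unblinded and, as described, without matching baseline questions. The article does not say how fewer is to be judged.

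The size is 0 of 5 target participants with a like-for-like comparison on this component, against up to 5 of 5 if the items are asked at both visits. Paired anxiety severity is planned for all 5.

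Severity is moderate: no confirmatory conclusion depends on the clause, and the anxiety half of it is measured at both visits. The finding assumes that the published schedule is complete with respect to instruments, and that the EASI measures what the article says it measures.

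**What to change.** Ask the avoidance items of the same diagnostic protocol at T2, in the same wording and mode as at T0. As an alternative or addition, give the four-level Phase 1 avoidance rating at T0 and T2 for the scenes in the participant's chosen set. That rating is not described as validated, so it should be reported descriptively.

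Avoidance alone is narrower than safety-seeking. Add a few matched questions at both visits on other safety behaviours, such as going out only with trusted people, which the Background section gives as an example. The same section sets apart behaviours that a neurologist has indicated for seizure safety, and the count should follow that distinction.

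State in Phase 3 Data Analysis that fewer is judged from these paired answers, participant by participant, with the exit interview as supporting qualitative evidence. Update Table 1 and Textbox 6 to match. If none of this is wanted, remove the safety-seeking component from the success rule.

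The cost is a few extra minutes per participant, a small added burden for about 5 people, and a minor ethics amendment.

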**Assessments**					
	Epilepsy Anxiety Survey Instrument	18	0-54	Higher scores suggest more severe anxiety	Scott et al [39]
	Brief Epilepsy Anxiety Survey Instrument	8	0-24	≥7 suggests a likely anxiety disorder	Scott et al [39]
	Perceived Stress Scale	14	0-56	Higher scores indicate greater perceived stress levels	Cohen et al [50]

## Results

This study was funded by a joint Junior Faculty Funds and Minor Research Grant from the York University Faculty of Health in November 2021. Recruitment for phase 1 was completed as of August 7, 2022, and had a final sample of 18 participants. Results for phase 1 will be published once data collection and analysis have been completed; data collected as of August 7, 2022, may be requested by contacting the corresponding author.

We are leveraging discussions with experts in the field to design the first VR-ET program specific to people with epilepsy which have led to some minor amendments (Textbox 7) to our original protocol.

Summary of study amendments to improve the study’s methodology.Phase 1 questionnaire*Updated* the wording and layout so that it would be faster, simpler, and more intuitive for participants to fill out.*Added* relevant questions, such as the specific prompts for each scene.Phase 1 informed consent form*Updated* the wording to remove any language that may have overstated the risks of filling out the questionnaire.*Adapted* it to be deliverable over a web-based platform.Phase 2 recordings*Updated* the guidelines so that common sensory triggers for seizures will be avoided. This was added after discussion with an epileptologist about the use of virtual reality in people with epilepsy.Phase 3 assessments*Added*: Epilepsy Anxiety Survey Instrument, Igroup Presence Questionnaire; System Usability Scale.*Removed*: Beck Anxiety Inventory; Generalized Anxiety Disorder-7 scale.Honorarium*Added* for phases 1 and 3.

## Discussion

### Principal Findings

Although the primary anxiety treatments for people with epilepsy are cognitive behavioral therapy and pharmacological treatments, minimal research has investigated anxiety treatments specifically for this population [51,52]. Moreover, few studies have investigated the use of ET for treating anxiety in people with epilepsy [24,25]. No studies to our knowledge have delivered ET to people with epilepsy using VR, despite VR-ET’s efficacy in other populations and the benefits that it could offer to people with epilepsy [11].

The main amendments made to the protocol included changes to the phase 3 anxiety assessments, after consultation with a clinical neuropsychologist who specializes in treating people with epilepsy. Indeed, when assessing anxiety in people with epilepsy, it is important to use validated assessments that do not inquire about physical manifestations of anxiety that may be confused with consequences of the neurological disorder. For example, the Beck Anxiety Inventory has been shown to be potentially less accurate in measuring anxiety in people with epilepsy because it contains items that reflect antiseizure medication side effects and symptoms of epilepsy, as opposed to symptoms of anxiety [39]. The Generalized Anxiety Disorder-7 scale was removed because it focuses on generalized anxiety disorder rather than anxiety in general or epilepsy-specific fears. Instead, the EASI was added.

The IPQ and SUS were also added to assess the feasibility of the intervention as well as provide validated feedback on participants’ experiences with the technology in preparation for the subsequent larger clinical trials. For example, the IPQ will help assess participants’ sense of presence in the virtual scene, which is important in VR-ET so that it resembles the real-life scenes that participants fear as closely as possible [18]. The IPQ will also be useful for determining if phase 2 was successful in realistically capturing the scenes. The interview at T2 will expand on responses to the IPQ as participants will be asked to provide verbal feedback on how future studies could improve the realism of the VR-ET scenarios, as well as the sense of presence that they generate. Furthermore, the SUS will provide useful information for optimizing procedures for training participants on how to use the VR equipment. The SUS may also help to identify if there were greater difficulties for people with cognitive deficits and inform how we could design a system that is accessible for all potential individuals with epilepsy. To assess motion sickness tendencies and symptoms after the VR-ET sessions, the VRISE and Fast Motion Sickness Scale were also included.

### Limitations

Pilot studies play a key role in the development or refinement of new interventions, assessments, and other study procedures, with the primary role of a pilot study being to examine the feasibility of a research endeavor [53]. Although the nature of a pilot study allows for a small sample size, we acknowledge that this is a limitation of both phases 1 and 3 and that, as a result, caution should be applied to the generalization of the findings. The sample sizes were determined based on resource constraints (funding and time) and are appropriate for a feasibility study that does not aim to assess clinical efficacy. To help account for the small sample size of phase 1, the baseline interview of phase 3 will act as an extension of phase 1 where we will gain more insight into the specific epilepsy- and seizure-related fears that people with epilepsy experience.

Another limitation to the generalizability of our findings is that phase 3 does not include a control group. Participants will be recruited to a known, albeit experimental, study and assessments will be conducted in an unblinded fashion. The choice to run an open-label pilot with no control group was intentional. Our primary goal is to report on the feasibility of recruitment, intervention design and implementation, as well as participant retention. Given the novelty of this initiative and our resources (funding and time), the research team agreed that this was the most appropriate way to systematically gather and incorporate user feedback before evaluating VR-ET on a larger scale. Future studies with larger sample sizes, a control group, and randomization will be necessary to evaluate clinical efficacy.

We acknowledge that it may not be feasible in clinical practice for therapists to have daily communication with their clients or patients. However, we are designing the intervention this way purposefully for the pilot study to maximize safety in case of a seizure or concerning psychological distress, such as a panic attack. In addition, as discussed with a clinical neuropsychologist, it will maximize the chances of therapeutic success if participants are in communication with someone, such as a therapist or researcher, while doing the exposures to help them form a behavioral commitment. Because this is a pilot study, it aligns more with the purpose of the research to maximize the chances of therapeutic success rather than to assess the feasibility of the proposed intervention within a professional setting. However, the ability to implement self-guided sessions in a controlled and safe virtual environment is an advantage of VR therapy. Therefore, future studies should investigate participants’ adherence to VR-ET and its efficacy when they perform the exposures daily without a researcher or therapist present.

Another limitation is that while we ask participants to avoid taking a benzodiazepine before performing the exposure and after their exposure until their anxiety settles, we cannot enforce this request because benzodiazepines may be used to treat seizures [34]. As previously discussed, taking a benzodiazepine can limit the effectiveness of the ET. It may be worthwhile to conduct future clinical trials in a safe and well-monitored environment, such as a hospital epilepsy monitoring unit, where participants are restricted from taking a benzodiazepine as much as possible. In this scenario, the participants would be in a safe environment in case they were to have a seizure and potential confounding effects would be reduced.

In conclusion, we are proposing a novel VR-ET as a treatment specific to people with epilepsy and their unique fears relating to their condition. VR is an especially promising tool for ET broadly as it allows for tailored exposure and control over the visual and auditory stimuli. When considering people with epilepsy, VR-ET offers additional advantages for this population. For example, given that the therapy can be administered in the comfort of one’s home, it increases accessibility for individuals with restricted independence and ability to travel. Overall, this study will contribute significantly to the fields of VR, ET, anxiety, and epilepsy and lay the groundwork for a more equitable therapy program for this population.

